**Fig. 2 Fig2:**
[figure not shown]
hypothesised intervention logical model for behavioural change (conceptual framework for the intervention)

### Step IV: Development of the intervention programme

The practical strategies were built into the intervention scope and sequence, Additional file 5. The intervention consists of five interactive group sessions, 150 min each, Fig. 3. A booklet (infographics); on benefits/recommendations, local vegetable recipes, and practical tips to eat more fruits, vegetables and do more PA is included as a guide, Additional file 6. Tools to assess PA and food environment for opportunities were included, Additional file 7. As well a self-monitoring tool for PA, fruit and vegetable intake was included for participants to track their behaviour daily goals for use in the feedback sessions, Additional file 8. The infographics were designed with locally recognisable images as cultural relevance of health promotion materials is vital for the success of an intervention [20]. Messages on the infographics were framed in a positive and active tone as evidence shows that positively framed messages are more acceptable [20].

**Fig. 3 Fig3:**
[figure not shown]
Showing delivery timeline of the intervention sessions, intervention content (organised practical strategies from step III), role of participants, and anticipated outcome per session

Brain storming workshop with planning group I and FGDs with the target group identified religious institution women group structures as an appropriate potential delivery channel. The women group structures boosts established social networks, community reach (85% Ugandans are Christians) and trust. The channel offers an opportunity for assessing the intervention effectiveness in an unrestricted real-life community setting.

“Religious institutions because they are transparent, religious organizations because they reach out to a bigger community and then they are transparent. The health centers, there is that rudeness, and still for health centers will only meet those people who come to them, but the church, you get a bigger audience”, “Come to churches like this, people really belong to this communities, then you say every third Saturday or Sunday of the month, from 4 to 5 pm, there will always be a nutritional class, for the first-time people may not come, but eventually they come, if it is a free class”, participants in FGD 4.

### STEP V: Adoption and implementation plan

The intervention will be delivered through institutional religious women groups (results of environmental asset assessment framework - see step IV). Through meetings with the strategic community leaders, a collaboration was established with Our Lady of Africa Catholic Parish, Mbuya. Mbuya Catholic Parish has six sub parishes. Within these sub parishes they are existing women groups, and these groups will be utilized for face-to-face intervention group sessions. FGDs with target group and meetings with planning group II pointed at the importance of opinion peer leaders being part of the implementation team.

“Our women group leader has helped us a lot, she taught us the dangers of cooking in polyethene bags and taught us the use of banana leaves, us we had got so much used to using the polyethene bags, she can’t eat the food you have prepared in polyethene bags, even if she visits you and if you have cooked like that, she can’t eat that food. “We have musawo (village health team) in our group, she usually brings for us education sessions on how to eat, she goes a lot for these education sessions and what she learns she brings them back to us”, participants in FGD 6.

Scientific evidence shows that the efficacy and acceptability of health promotion interventions increases if peer opinion leaders within the target group are part of the implementation team [38]. Peer opinion leaders provide entry and legitimacy to the external change agents and may help drive changes in social norms. Selection of peer opinion leaders: the intervention will be delivered within existing women groups. Leaders of these existing groups will be selected to work as peer opinion leaders on the implementation team. The main role and responsibilities peer opinion leaders will be to (i) mobilize fellow women to participate in the intervention, (ii) follow up and (iii) give social support to participating women to attain set intervention goals. Women leaders will be given a two - day refresher training on mobilization and leadership skills, as mobilization is the routine responsibility for women leaders in their usual group meetings. The planning group I designed the sessions to be moderated by health behavior coach (PhD researcher) following the techniques of motivational interviewing [39]. A general guide (scope & sequence) will ensure consistency during the group sessions.

### Step VI: Development of an evaluation plan

#### Study design, setting and timing

The effectiveness of the intervention will be evaluated through a cluster-randomized controlled trial. The intervention will be evaluated in Kampala, the capital city of Uganda. The six sub parishes of Mbuya catholic parish will be randomized to treatment and control arms, Fig. 4. The treatment arm will be exposed to both the developed intervention infographics and face to face group sessions while the control arm will only receive the developed intervention infographics. An awareness session will be organized to distribute the infographics to the control arm. Within the sub parishes, there are existing women groups. These existing groups will be utilized for face-to-face intervention group sessions. For the intervention purposes, each group will be limited to a maximum of 14 members. The study period is divided into two phases: a three-month intervention and a three-month post-intervention follow-up phase.

**Fig. 4 Fig4:**
[figure not shown]
Study design

### Recruitment

The PhD researcher and women leaders of existing groups will make presentations about the intervention during one of the routine meetings. Flyers with details of the intervention will be distributed for sharing with members who are absent during the briefing. At the end of the presentations, interested participants will be invited for the first session to test their eligibility to participate in the study. Eligible participants will be provided with an informed consent form to endorse.

#### Inclusion criteria

i)Sex (women),ii)Age (18 to 45 years),iii)Central obesity [waist circumference ≥ 80 cm]),iv)Fluent in either Luganda or English (sessions will be conducted in Luganda/English).v)Willingness to follow the three-months intervention and three months follow-up,vi)Willingness to sign the informed consent.

#### Exclusion criteria

i.Being treated for diabetes Mellitus Type 1 or Type 2, hypertension, high cholesterol, or any other cardio-metabolic related disease.ii.Pregnancy.

### Outcomes

Primary outcome is reduction in waist circumference. Decreases in waist circumference are recommended as critically important treatment target for reducing adverse cardiometabolic health risks [15]. Secondary outcomes include optimisation of, fasting blood glucose, total cholesterol, HDL, LDL, triglycerides, body composition, food literacy, PA, and fruit and vegetable intake.

### Sample size calculation

Sample size calculation is based on waist circumference.

To calculate the sample size, we used the formula described by Rutterford, Copas [40], Table 3.

**Table 3 Tab3:** Description of sample size calculation

$$\boldsymbol{m}=\frac{{\left({\boldsymbol{Z}}_{\mathbf{1}-\boldsymbol{\alpha} /\mathbf{2}}+{\boldsymbol{Z}}_{\mathbf{1}-\boldsymbol{\beta}}\right)}^{\mathbf{2}}\ \mathbf{2}{\boldsymbol{\sigma}}^{\mathbf{2}}}{{\boldsymbol{\Delta}}^{\mathbf{2}}}\left(\mathbf{1}+\left(\boldsymbol{n}-\mathbf{1}\right)\boldsymbol{\rho} \right)$$	
where? m = sample size per study arm	= 1.96 at the type 1 error of 5% = 0.842 at 80% power
σ = the standard deviation of primary outcome in the population	• Based on Uganda STEP survey [2], the standard deviation of waist circumference for women aged 18 to 49 years = 13.73.
△ = effect size = 7.4cm.	• Effect size was calculated based on Bendall, Mayr [41] , impact of the Mediterranean diet on central obesity. • Only studies with a duration below 12 months were included in the calculation as the proposed study duration is below 12 months.
(1 + (*n* − 1)*ρ*)= design effect (DE) to compensate for cluster randomisation. ▪ n = number of individuals per cluster ▪ ρ = Intra-Cluster Correlation coefficient	• For our intervention, n = 27 • ρ = 0.001 ▪ There is no data available on the intra-Cluster Correlation coefficient of waist circumference across villages for communities within Kampala. A range of 0.001 to 0.10 is demonstrated as a cost - effective and safe choice to account for the variability.

m = (1.96 + 0.842)^2^ *2*13.73^2^/7.4^2^) * (1 + (27-1) *0.001)

m = 55 participants

To cover for dropouts, m is increased by 20%, to make 66 participants.

Hence, the project aims to include 132 women in the trial, 66 in the treatment arm and 66 in the control arm

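### The stated 80% power is not supported by the sample-size calculation for three clusters per arm: on the printed inputs it is about 55% at ICC 0.001 and 26% at ICC 0.10

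*Protocol article*

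**What the plan says.** Under Study design, setting and timing, the article states that "The six sub parishes of Mbuya catholic parish will be randomized to treatment and control arms". The Randomization section fixes a 1:1 allocation of these clusters, hence three per arm.

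Table 3 (Sample size calculation) takes its quantiles as "1.96 at the type 1 error of 5% = 0.842 at 80% power". It uses "the standard deviation of waist circumference for women aged 18 to 49 years = 13.73", "effect size = 7.4cm", 27 women per cluster and ICC 0.001. It acknowledges that no ICC is available for waist circumference in Kampala communities and then says: "A range of 0.001 to 0.10 is demonstrated as a cost - effective and safe choice to account for the variability". The result is 55 women per arm, raised by 20% to 66 per arm, 132 in all.

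On the comparator, the article says that "the control arm will only receive the developed intervention infographics". The treatment arm receives the same infographics plus the group sessions. The 7.4 cm comes from a review described as "impact of the Mediterranean diet on central obesity".

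The Data analysis section plans a linear mixed model with time, treatment, their interaction and age as fixed effects, and sub parish and participant as random factors.

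**The concern.** Two choices in the calculation both push the stated power upwards.

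- **Reference distribution.** Treatment varies only between sub parishes. With six of them, the variation against which the effect is judged is estimated from very few units. Normal quantiles treat that variation as known, as if there were many clusters.
- **ICC.** If no estimate exists and a whole range is called safe, taking the bottom of it is the least cautious choice. The design effect of 1.026 removes almost all of the correction for clustering.

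This is the only power statement for the primary outcome. The Discussion and Conclusions link later adoption to whether this trial shows effectiveness, so readers will lean on the 80% when they interpret a non-significant result.

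**Working it through.** **Reproducing the article's figure.** Before clustering: (1.96 + 0.842)² × 2 × 13.73² / 7.4² = 54.06 per arm. Design effect: 1 + (27 − 1) × 0.001 = 1.026. Product: 54.06 × 1.026 = 55.46, printed as 55. Then 55 × 1.2 = 66. The multiplication is sound; the question is whether the formula fits the design.

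**Inputs for the check.** SD 13.73 and difference 7.4 cm (Table 3); three clusters per arm (six, 1:1); 66 recruited less 20% = 52.8 evaluable per arm, so 52.8 / 3 = 17.6 per cluster. The printed 27 per cluster does not match the article's own totals (66 / 3 = 22 recruited, 55 / 3 ≈ 18 evaluable), so the actual cluster size is used here.

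**Formulas.**
- Degrees of freedom: 2 × (3 − 1) = 4; two-sided 5% critical value 2.776.
- Design effect: DE = 1 + (m/3 − 1) × ICC.
- Standard error: SE = 13.73 × √(2 × DE / m).
- Power: noncentral t with 4 df and noncentrality 7.4 / SE. For comparison, normal power is Φ(7.4 / SE − 1.96).

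**Example, ICC 0.001.** DE = 1 + 16.6 × 0.001 = 1.0166; SE = 13.73 × √(2 × 1.0166 / 52.8) = 2.694 cm; 7.4 / 2.694 = 2.747. Normal power is Φ(0.787) = 78%; on 4 df it is 55%.

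| ICC | DE | SE (cm) | Power, normal quantiles | Power, t with 4 df |
|---|---|---|---|---|
| 0.001 | 1.017 | 2.69 | 78% | 55% |
| 0.01 | 1.166 | 2.89 | 73% | 50% |
| 0.05 | 1.830 | 3.61 | 53% | 35% |
| 0.10 | 2.660 | 4.36 | 40% | 26% |

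**Sensitivity.**
- With 55 evaluable per arm, the 4-df column reads 56%, 51%, 35% and 26%. With all 66 retained it is 64% at ICC 0.001 and 27% at 0.10.
- With 55 per arm and the printed 27 in the design effect, it is 56% and 21% at the two ends of the range.
- Simulated cluster-mean t-tests with 18 women per cluster gave 55.9% and 26.0% at the two ends.
- The article's own formula at ICC 0.10 gives 54.06 × (1 + 26 × 0.10) = 54.06 × 3.6 ≈ 195 per arm, so the ICC choice matters even if the degrees of freedom are left aside.

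**What the printed inputs leave out** (assumed values, since the article gives none; 52.8 per arm, 4 df):
- *Baseline adjustment.* Multiplying the variance by 1 − r², at both levels, gives for r = 0.7 power of 82%, 58% and 44% at ICC 0.001, 0.05 and 0.10. For r = 0.9 it is 99%, 93% and 82%.
- *Eligibility.* The SD describes women aged 18 to 49 in a survey, but the trial enrols only women with a waist of at least 80 cm. If the survey distribution were normal with mean 80, 85, 90 or 95 cm, truncation at 80 cm would give an SD of about 8.3, 9.2, 10.2 or 11.1. Without baseline adjustment, power would then be 92%, 86%, 79% or 72% at ICC 0.001, and 57%, 49%, 42% or 36% at ICC 0.10.

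**The case against.** The strongest reply is that the calculation above is not the planned analysis. Waist circumference is measured at all three visits and the mixed model includes baseline. Eligibility also narrows the SD. Either could bring power to about 80% or more at ICC 0.001, even on 4 df. This stands. A reader might infer that the trial's real power is 55%, or 26%, and that 80% will certainly not be reached; the documents do not support that, because the two figures hold for the printed inputs only.

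A second reply is that 4 df belongs to a cluster-level test and the article names no method for degrees of freedom, which it may leave to a fuller plan. A model with random intercepts only could also give the time-by-treatment interaction many more. But such a test is valid only if change varies little between sub parishes, and with six clusters a normal reference does not protect the type I error once the ICC is not negligible. If the ICC really were 0.001, power near 78% would be fair on the printed SD, but the article says it has no data to show this.

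Third, 0.10 is the end of a range and not an expected value. That is so, which is why the whole range should be shown. Power already falls to 50% at ICC 0.01.

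A reader might also infer that 7.4 cm is wrong because it comes from Mediterranean-diet studies while both arms receive infographics. The source figures are not shown, so this cannot be established. The contrast only needs to be named correctly.

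**Conclusion.** The concern holds in this form: the printed 80% does not follow for a trial with three clusters per arm. On the article's SD and difference, with 52.8 to 55 evaluable women per arm and no baseline adjustment, power is 55–56% at ICC 0.001 and 26% at ICC 0.10. Even with normal quantiles and 52.8 per arm, it drops from 78% to 40% across the range the article calls safe. The figures rest on equal cluster sizes and a test with 4 df.

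Power under the planned mixed model cannot be determined from the article. It may be adequate at a very small ICC, and at larger ICCs that depends on a baseline correlation and an SD that are not stated. The fault lies in the justification given, not in the multiplication, and it is no proof that the trial is too small.

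**What to change.** In the sample-size section, replace the single 80% statement with a power table based on the t distribution with 4 df for ICC 0.001, 0.01, 0.05 and 0.10, using the cluster size that the enrolment target implies. State the SD assumed for women who meet the waist criterion. If baseline adjustment is relied on, state the assumed correlation and compute power for that analysis. Describe the contrast as group sessions plus infographics versus infographics alone.

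The cost is a revised paragraph and a stated power that may be less favourable. Recruitment and design do not change.

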### Randomization

The six sub parishes (clusters) will be listed alphabetically. A cluster randomization with a 1:1 allocation will then be applied to randomize the sub parishes to either the treatment or control arm. In the sub parishes, women group leaders and participants will be blinded about the study arms.

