**Fruit and vegetable intake, food literacy and physical activity**				
Fruit and vegetable intake	Fruit and vegetable intake screener adapted from NIH screeners (https://epi.grants.cancer.gov/diet/screeners/fruitveg/instrument.html) , Additional file 9 Food literacy questionnaire (developed by our research team for Ugandan context in consideration of Poelman, Dijkstra [29] and Vidgen HA [27]. We are currently validating the questionnaire, Additional file 10	X	X	X
Food literacy		X	X	X
Physical activity (self-reported)	Short version of International Physical Activity Questionnaire (IPAQ-SF)	X	X	X

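### The stated blinding of group leaders and participants conflicts, as worded, with the rest of the design, so the self-reported secondary outcomes lack the protection it implies

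*Protocol article*

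**What the plan says.** The claim stands without qualification in the protocol article, section Randomization: "In the sub parishes, women group leaders and participants will be blinded about the study arms".

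The section Study design, setting and timing defines the arms: "The treatment arm will be exposed to both the developed intervention infographics and face to face group sessions". The comparison group has no such sessions and is given the printed material alone. The article describes its delivery as follows: "An awareness session will be organized to distribute the infographics to the control arm". Step IV of the Results gives the content of the treatment arm: "The intervention consists of five interactive group sessions, 150 min each".

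On the leaders, Step V says: "Leaders of these existing groups will be selected to work as peer opinion leaders on the implementation team". It gives them the tasks of bringing women into the programme, following them up and encouraging them towards its goals. Under Recruitment, they present the intervention together with the PhD researcher. The limitations part of the Discussion adds that women group leaders took part in developing the intervention and are expected to help carry out the evaluation.

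The primary outcome is waist circumference, taken by tape. Among the secondary outcomes, Table 4 labels physical activity as self-reported (IPAQ short form), takes fruit and vegetable intake from a screener, and takes food literacy from a questionnaire developed by the team. All three are collected at baseline, after the three-month intervention and after three further months.

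**The concern.** The article claims a property that its own description of the arms and of the leaders' role does not support. A reader who takes the sentence at face value will assume that women answer the activity, diet and food literacy questions without knowing which programme they are in. That assumption guards against one specific error, namely women in one arm reporting more favourably because of what they were taught and asked to pursue.

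The sessions use goal setting, daily self-monitoring of activity and of fruit and vegetable intake, and feedback on that monitoring. The follow-up questionnaires then ask about the same behaviours. If reporting shifts more in the session arm than in the infographics arm, the trial could show an apparent gain in behaviour that is partly a gain in reporting. At stake is how much weight those three outcomes can carry. The sample size and the primary analysis are not affected.

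**Working it through.** The point turns on no figure in the plan, so the check sets the sections side by side.

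**1. Can participants be unaware of what they receive?**
- Treatment arm: infographics plus 5 sessions × 150 min = 750 min of face-to-face contact (Step IV), including a practical group cooking session (Step III) and a self-monitoring tool (Step IV).
- Control arm: the same infographics, handed out at an awareness session of unstated length (Study design, setting and timing).
- No sham or attention-matched sessions are described.
- Before enrolment, women hear presentations about the intervention and flyers with its details circulate (Recruitment). To be eligible they must be willing to follow the three-month intervention and the follow-up (Inclusion criteria).

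Every participant can see whether she attends a course of sessions or receives a booklet. What she might not know is what another sub parish receives.

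**2. Can leaders be unaware?**
- They present the intervention (Recruitment).
- They sit on the implementation team and support women towards its goals (Step V).
- Some took part in its development (Discussion). Representatives of the collaborating religious institutions helped to settle on group sessions as the delivery format (Step III), and the materials were pretested with them (Step IV).
- All six sub parishes belong to one parish (Step V).

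A leader who helped to design group sessions, and whose own sub parish gets only infographics, would recognise the control arm.

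**3. Which outcomes are exposed?**

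| Outcome | Source (Table 4) | Depends on the woman's own report |
|---|---|---|
| Physical activity | IPAQ short form | Yes, labelled self-reported |
| Fruit and vegetable intake | Screener | Yes |
| Food literacy | Questionnaire | Yes |
| Waist circumference (primary) | Tape, twice | No |
| Glucose, lipids, body composition | Devices | No |

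**4. Does the analysis remove the problem?** Data analysis plans linear mixed models with time, treatment and their interaction, the interaction being spelled out for metabolic health. For a self-reported outcome, let δ be the true difference between arms in change from baseline. Let b_T and b_C be the shift in reporting from baseline in the treatment and control arms. The interaction then estimates

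δ + (b_T − b_C).

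A reporting habit that is constant over time cancels against baseline. A shift that begins with the sessions does not cancel, and adjusting for clustering does not touch it. The article gives no value for b_T or b_C, so the size of b_T − b_C cannot be computed.

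**The case against.** The strongest defence is that being blinded about the study arms need not mean being unaware of one's own programme. Allocation is by sub parish and both arms receive something active. Women could know what they get without knowing that another sub parish gets something else, or which arm is under test. The article does not say whether the recruitment presentations disclose two arms, or whether they precede allocation. This reading may hold for some participants, so it would go too far to call blinding impossible in every sense. It does not hold for leaders who helped to develop the intervention. Nor would it protect the self-reported outcomes, because a woman's reporting can shift with the programme she has attended whether or not she knows of another.

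Further points stand in part:
- The infographics, with recommendations and tips, go to both arms, so controls also learn what is recommended. This narrows the difference in reporting but does not remove it.
- Food literacy is meant to rise, so a higher score may be the intended effect. It may also be partly reporting, and the design cannot separate the two.
- The leaders' two-day refresher covers mobilisation and leadership, not the content of the arms. The point therefore does not rest on their training.
- The article does not list blinding among its strengths, and the self-reported outcomes are only secondary. This limits the harm but leaves the sentence wrong as worded.

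A reader might also infer that the tape-measured primary outcome is presented with protection it lacks. The document does not support that. The main safeguard for a tape reading is masking of the measurer, on which the sentence is silent, and a condensed article may leave that to the full protocol. Nor does the article say that the coach or the leaders will take measurements.

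**Conclusion.** The point holds as a conflict within the article. The blinding sentence, as worded, cannot be squared with the arms as described or with the leaders' role. The consequence is confined to three secondary outcomes: physical activity, fruit and vegetable intake and food literacy. For these, differences between arms are open to reporting bias of unknown size.

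The conclusion assumes that no sham or matched-attention sessions exist (none are described) and that the leaders who helped in development include at least some from the trial's own groups, as the Discussion suggests. Confidence is high on the inconsistency. That bias will actually occur is a reasoned expectation, not something the article shows. Nothing here says that the document asserts masked assessment of waist circumference, and no change to sample size, endpoints or model follows.

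**What to change.** Replace the sentence in Randomization with a statement of what is concealed, from whom and until when. Depending on what was intended, examples are:
- allocation is concealed from leaders and women until recruitment and baseline measurement in all sub parishes are complete; or
- participants are not told the content of the other arm.

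The first protects recruitment and baseline data. Neither protects follow-up self-report.

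Then describe the trial as open to participants, group leaders and the session coach. State that differences between arms in the three questionnaire-based outcomes will be read as supportive and open to reporting bias.

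Where the existing data-collection team allows, the session coach and a group's own leader should not take the waist measurements or conduct the interviews at the two follow-up visits. This is a precaution, not the correction of a stated error.

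Cost: the wording change is negligible, at the price of a weaker stated design. The rostering adds some constraint. How much cannot be said, because the article does not describe who collects the data.
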